A quite recent study affirms that the prevalence of GAD in the general population might actually be as high as 5 to 8% [2], while among individuals seeing their physicians for psychological problems the 25% of them have a diagnosis of pure GAD. Indeed, in primary care facilities, GAD is the most frequent anxiety disorder and the second most frequent of all mental disorders [3,4]. GAD is more prevalent in women and much more prevalent in youths, where 12% to 20% are affected [5-7]. The age of onset is between the late teens and early twenties and the average duration is about 20 years, suggesting a chronic and fluctuating course that often worsens during time of stress. People with general nervousness, depression, inability to tolerate frustration, and feelings of being inhibited are more likely to be shown in GAD patients. People with GAD tend to have more conflicts with others, are very hard on themselves, and tend to avoid common situations for fear of worry and anxiety. In youths, GAD often leads to lower levels of social supports, academic underachievement, underemployment, substance use and high probability of developing other psychiatric disorders. In epidemiological studies of GAD a consistent finding has been that over 90% of individuals who meet criteria for GAD in a given year will also have at least one other DSM-IV diagnosis [8].

The high prevalence of GAD in the general population and the severe limitation it causes, point out the necessity to find new strategies to treat it in a more efficient way. GAD is usually treated with medications and/or psychotherapy. In particular, the two most promising treatments seem to be cognitive therapy and applied relaxation. As shown by numerous studies, both of these treatments are equally effective [9,10] immediately and over long-term periods. Cognitive treatment helps patients to recognize and alter patterns of distorted thinking and dysfunctional behaviour, while relaxation serves to reduce the increased physical arousal often strictly associated to this disorder. In fact, physical arousal can be voluntarily altered with training in relaxation skills that enables patients to shift physical functions voluntarily toward those that naturally occur in a relaxed state [11]. Progressive muscle relaxation and more general imagery techniques can be used as therapy progresses since the ability to relax, and to do it in any place or situation, is vital to reduce the anxiety level.

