### Aim of the study

Knowing that relaxation techniques are as effective as cognitive and behavioural methods in the treatment of GAD and considering the critical point regarding the difficult in learning them, the aim of the present study is to investigate the advantages of using a VR-based relaxation protocol in reducing anxiety in patients affected by GAD. The following hypothesis will be tested:

I) GAD patients exposed to a VR relaxing environment learn how to relax themselves easier and more efficiently than patients exposed to a traditional relaxation protocol;

II) There is a positive correlation between the treatment efficacy and the sense of presence experienced by the patients during the treatment sessions.

3-D audio-visual experiences, whose critical aspect is to induce a feeling of presence and engagement, will be presented to the subjects in order to help them to become relaxed. Through the link between the feeling of presence and the emotional state, VR relaxing environments will be used to reduce the anxiety levels in their users [15].

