### Subjects

Patients will be recruited in a public health-care structure in Milan, Italy, according to the diagnosis received from their treating responsible psychiatrist or psychologist. In order to be included in the study, patients have to meet the following criteria: (1) primary diagnosis of GAD; (2) requesting treatment for their GAD; (3) older than 17 and younger than 70; (4) no depressive disorder preceding the current episode of GAD or requiring immediate treatment; (5) no behaviour therapy received for their GAD; (6) no evidence of organic mental disorders accounting for the complaints, mental retardation, psychotic disorders, alcohol or drug dependence; (7) no migraine, headache, seizure disorder, and vestibular abnormalities since they represent significant contraindications for the use of VR.

A power analysis was conducted in order to evaluate the number of patients needed to detect a significant difference (Effect size f ≥ 0,40) between the three groups (VR, non VR and WL) with a power of 0,90. The analysis showed a necessary total sample size of 75, 25 in each group, with α = 0,5, two-tailed. Both males and females will be included. All participants have to be clinically stable, meaning no change in dose of psychotropic medications 1 month before inclusion. Since over 90% of individuals who meet criteria for GAD in a given year will also have at least one other DSM-IV diagnosis [8], patients will be included in the study even if they present at least one more psychiatric diagnosis.

Before participating in the study, each patient will be provided with written information about the study and invited to give written consent for inclusion. The present research is in compliance with the Helsinki Declaration.

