### Trial analysis

Data will be entered in SPSS. Descriptive methods will be used to demonstrate the consistency of the three groups, describe participant characteristics and report levels of participation and drop out. Analysis of variance will be used to evaluate baseline characteristics of the three groups involved in the study, overall significance of improvement across outcome measures, and drop out versus maintainers. For each patient, change in psychometric and physiological measures will be calculated and analysed using t-test for matched groups for both intervention and control groups. The magnitude of change will be estimated and the 95% confidence intervals given.

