## Discussion

Despite a large number of studies showing the advantages of using VR for the treatment of anxiety disorders (for a recent review see [30]), up to date there is only one study about its potential in stress management and relaxation processes in a sample of non-clinical stressed subjects [15]. What we would like to show with the present study is that VR can facilitate the reduction of anxiety even in a sample of GAD patients. We believe that the use of immersive VR for relaxation represents a promising approach since it enhances the quality of the relaxing experience through the elicitation of the sense of presence. In fact, as reported by different studies [31-34], individuals who interact in environments enriched with a variety of positive visual and auditory stimulations, report greater improvement in self-efficacy and mood. Being able to become relaxed in a certain situation promotes the sense of self-efficacy and prepares participants to cope with real anxiety situations.

Our outcome measures are well-suited to measuring both the subjective and objective impact related to the intervention and the presence of a non-VR group and of a WL list group will guarantee that the results eventually found are really attributable to the intervention. This controlled trial will be able to evaluate the effects of the use of VR in relaxation while preserving the benefits of randomization to reduce bias. Its design takes into account the need for internal and external validity and that the results are attributable to the intervention. Since the international scientific community is now starting to widely recognize the potential of VR as clinical tool [35] we look forward to adding the results of this trial to the growing body of literature in this area.

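### The only test of change that the article spells out, and on the natural reading its only 95% intervals, are within-arm, although hypothesis I compares VR with non-VR

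*Protocol article*

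**What the plan says.** All references are to the protocol article.

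- **Trial analysis** gives two inferential tools for outcomes. Analysis of variance is assigned, among other uses, to "overall significance of improvement across outcome measures, and drop out versus maintainers". Per-patient change in the psychometric and physiological measures is "analysed using t-test for matched groups for both intervention and control groups".
- The same section ends: "The magnitude of change will be estimated and the 95% confidence intervals given". It names no difference between arms as the quantity to be estimated.
- **Aim of the study**, hypothesis I, is comparative: VR patients "learn how to relax themselves easier and more efficiently than patients exposed to a traditional relaxation protocol".
- **Subjects** sizes the trial for a difference across the arms ("Effect size f ≥ 0,40) between the three groups (VR, non VR and WL"), "with a power of 0,90", with 25 patients per arm.
- **Background** describes the illness as "suggesting a chronic and fluctuating course that often worsens during time of stress".
- **Discussion** says that the two comparison groups make the results attributable to the intervention, and that the trial can "evaluate the effects of the use of VR in relaxation while preserving the benefits of randomization to reduce bias".

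**The concern.** A matched t-test on a patient's own before and after values asks whether that arm changed. It does not ask whether the treatment caused the change, or whether one treatment did better than another. An interval for that change mixes any treatment effect with natural fluctuation and regression to the mean. The random allocation separates these only when arms are compared with each other.

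Hypothesis I needs an estimate of VR minus non-VR. As written, the article attaches its explicit test and, on the natural reading, its intervals to a different quantity. The remaining tool, the analysis of variance, is too loosely described to show that it fills the gap. The trial could then report a significant change in VR with a neat interval, and readers could take that as evidence of efficacy or of an advantage for VR. The attribution to the intervention that the Discussion claims would not follow from it.

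**Working it through.** **Inputs.** From Subjects: 25 per arm, f = 0.40, power 0.90. Alpha is printed as 0,5; I assume 0.05, two-sided. The article gives no figure for change without treatment, so I assume a standardised mean change dz (mean change divided by SD of change) of 0.2 to 0.6, identical in the arms compared. I also assume normal changes and complete data.

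**1. The article's own figure.** Power of a one-way ANOVA with k = 3 is P(F′ > F crit), where F′ is noncentral F with 2 and N − 3 degrees of freedom and noncentrality f²N. For N = 75, f²N = 0.16 × 75 = 12, and power is 0.869. Reaching 0.90 takes N = 84. The stated 75 is therefore not reproduced at alpha 0.05. That is a separate matter, and nothing below depends on it.

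**2. What an omnibus rejection would mean for hypothesis I.** Let VR and non-VR be exactly equal and both differ from WL by d SD. Then f² = (2/9)d², so f = 0.40 gives d = 0.40 / √(2/9) = 0.85. The noncentrality is the same as in step 1, so the omnibus test rejects in 87% of trials although VR has no advantage over non-VR.

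**3. Within-arm verdicts when VR and non-VR change equally.** The chance that one arm shows significant improvement is p = P(T′ > 2.064), where T′ is noncentral t with 24 degrees of freedom and noncentrality dz√25 = 5dz. The arms are independent, so the chance that VR is significant and non-VR is not is p(1 − p).

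| Assumed dz in both arms | p, one arm significant | VR significant, non-VR not |
|---|---|---|
| 0.2 | 0.159 | 0.159 × 0.841 = 0.134 |
| 0.3 | 0.302 | 0.302 × 0.698 = 0.211 |
| 0.4 | 0.484 | 0.484 × 0.516 = 0.250 |
| 0.5 | 0.670 | 0.670 × 0.330 = 0.221 |
| 0.6 | 0.821 | 0.821 × 0.179 = 0.147 |

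A direct two-sided 5% test of VR against non-VR would favour VR wrongly in 2.5% of trials, whatever the common change. The p column applies equally to a WL arm that improves without treatment.

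**4. A between-arm test on the same data.** In 20,000 simulated trials with no treatment effect, a three-arm ANOVA on change scores rejected in 5.0% (dz 0.4) and 5.2% (dz 0.5). A common change does not disturb it.

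**5. Precision, in units of the SD of change.**
- Within one arm: 2.064 / √25 = 0.413.
- Difference between two arms: 2.011 × √(2/25) = 0.569.
- Ratio: 0.569 / 0.413 = 1.38, about 1.4.

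**The case against.** **The plan does contain a tool that may be between-arm.** A reader might infer that every stated test is within-arm and that the randomization is thrown away. The article does not support that. It plans an ANOVA of improvement, in a sentence that also refers to the three groups, and it sizes the trial with an effect size across those groups. A between-arm ANOVA with matched t-tests as a supplement is a fair reading. This part of the objection stands. It does not settle the matter, because the factor is unstated and step 2 shows that an omnibus result cannot answer hypothesis I.

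**Contrasts may be in a fuller document.** Their absence from an article is not a fault, and I do not count it as one. The point is what the article does state: a test and an interval target that do not fit its hypothesis.

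**No faulty decision rule is written down.** A reader might infer that VR will be declared superior because VR is significant and non-VR is not. No section says so. The percentages in step 3 show what would happen if readers compared the verdicts that way; they are not an error rate of a stated rule.

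**Improvement in every arm is not established.** The Background describes a chronic as well as fluctuating course. Subjects sets no minimum symptom score and requires stable medication. Untreated improvement is plausible in patients who enter while asking for treatment, but the article neither quantifies nor asserts it.

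**A reading of matched groups as patients paired across arms** is also possible, but the calculation of change for each patient points to before-and-after pairing.

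**Conclusion.** The concern holds in a limited form. The only explicitly described test of change is within-arm, and so, on the natural reading, are the only stated 95% intervals. Neither answers hypothesis I or supports the attribution made in the Discussion. The ANOVA may be a between-arm test, but it is not specified well enough to repair this, and an omnibus rejection can come from WL alone (87% in the case worked above, at an assumed alpha of 0.05).

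The size of the risk from comparing within-arm verdicts, about 13% to 25% against 2.5%, rests on the assumed common change of 0.2 to 0.6 SD and on readers making that comparison. The mismatch between the stated analysis and the hypothesis does not depend on either assumption.

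**What to change.** Replace the matched t-test sentence and the interval sentence with wording such as:

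> Change will be compared between randomized arms. For hypothesis I the effect is the difference in change, VR minus non-VR. For the psychometric outcomes, each active arm minus WL is also estimated at the time points where WL is assessed. Each difference is given with its 95% confidence interval. Physiological and other session-based measures are compared between VR and non-VR only. Within-arm changes may be reported as description; no claim of efficacy or superiority rests on them.

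The limits on the WL contrasts follow from the design. Physiological measures and the visual anxiety rating are taken around treatment sessions, which WL does not have. The Data collection section gives WL a 12-month review but no 6-month one, whereas Psychometric assessment lists both follow-ups for every patient. The two sections should be reconciled before a 6-month contrast with WL is promised.

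**Cost.** Analysis wording only, with no added patients, visits or measurements. The reported intervals become about 1.4 times wider than within-arm ones (half-width 0.57 against 0.41 SD of change), which is the real precision for the question asked.

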## Discussion

Despite a large number of studies showing the advantages of using VR for the treatment of anxiety disorders (for a recent review see [30]), up to date there is only one study about its potential in stress management and relaxation processes in a sample of non-clinical stressed subjects [15]. What we would like to show with the present study is that VR can facilitate the reduction of anxiety even in a sample of GAD patients. We believe that the use of immersive VR for relaxation represents a promising approach since it enhances the quality of the relaxing experience through the elicitation of the sense of presence. In fact, as reported by different studies [31-34], individuals who interact in environments enriched with a variety of positive visual and auditory stimulations, report greater improvement in self-efficacy and mood. Being able to become relaxed in a certain situation promotes the sense of self-efficacy and prepares participants to cope with real anxiety situations.

Our outcome measures are well-suited to measuring both the subjective and objective impact related to the intervention and the presence of a non-VR group and of a WL list group will guarantee that the results eventually found are really attributable to the intervention. This controlled trial will be able to evaluate the effects of the use of VR in relaxation while preserving the benefits of randomization to reduce bias. Its design takes into account the need for internal and external validity and that the results are attributable to the intervention. Since the international scientific community is now starting to widely recognize the potential of VR as clinical tool [35] we look forward to adding the results of this trial to the growing body of literature in this area.

## Abbreviations

GAD – Generalized Anxiety Disorder; VR – Virtual Reality; WL – Waiting List group; PSWQ – Penn State Worry Questionnaire; BAI – Beck Anxiety Inventory; Anti – Anxious Thoughts Inventory; CID – Anxiety and Depression Scales of the Clinical Interview for Depression; STAI – State-Trait Anxiety Inventory; VAS-A – Visual Anxiety Scale; EMG – Electromyography; BVP – Blood Volume Pulse; SCR – Skin Conductance Response
